## Abstract

This is a study protocol for a pilot three-armed randomized controlled trial on nonsurgical integrative Korean medicinal treatment for symptomatic lumbar spinal stenosis (LSS). Thirty-six participants who have been diagnosed with (LSS) and recommended for spinal surgery by neurosurgeons or orthopedics and have had spinal symptoms such as severe low back pain and neurological claudication regardless of at least three months of conservative treatments will be recruited. Participants will be randomly assigned to be one of the three intervention groups, including the Mokhuri treatment program group 1 or 2 or usual care group. All treatments will be administered in inpatient units over a period of 4 weeks. The primary outcomes are 0 to 100 Visual Analogue Scales for low back pain and leg pain and the secondary outcomes are Oswestry Disability Index; EQ-5D; Roland-Morris Disability Questionnaire; Oxford Claudication Score; physical function test, including treadmill test, walking duration, and distance assessment for free leg pain; radiologic testing; and adverse events which will be assessed during the 4-week treatment period as well as after 3 and 6 months of follow-up. Then, we will assess the feasibility of the clinical trial design as well as a nonsurgical integrative treatment program. This trial is registered with CRIS registration number: KCT0001218.

## 1. Backgrounds

Lumbar spinal stenosis (LSS) is defined as narrowing of the central canal or neuroforamina, which is identified by radiologic imaging or intraoperational observation [1]. Among several different pathologic causes of LSS, degenerative changes in various structures around the spinal canal or neural foramina including the vertebral disks, facet joints, ligamentum flavum, posterior longitudinal ligament, and lamina are the leading cause of LSS [1]. Based on the Wakayama spine study, the prevalence of LSS is estimated as 10% in all age groups, with a prominent increase in the prevalence reported in those who are over 60 years old, which reflects that LSS is closely related to the degenerative changes [2].

In Korea, no precise information is available on the prevalence of LSS. However, according to the annual report of Health Insurance Review & Assessment Service, approximately one million patients who are diagnosed with LSS visit the hospital; as a result, LSS was ranked as the 56th most frequent cause for all hospital visits in Korea during 2011 [3]. In addition, the total number of hospital admissions for LSS has increased from 11,471 cases in 2000 to 78,372 in 2011 [3].

Spinal fusion surgery and decompression surgery are accepted as the standard treatments for spinal stenosis, and complex fusion surgery involving more than two levels of vertebral disc is more commonly practiced than before [4]. Spinal fusion surgery and decompression surgery were reported as effective during one to two years after surgery, but there is no concrete evidence on the increased effectiveness of these surgeries compared with nonsurgical conservative therapies in the long term [5]. The cost of surgery is considerably higher and there are frequent, severe adverse events related to surgery [4, 6]. In addition, nonsurgical conservative treatments of conventional medicine including drug therapy (acetaminophen, analgesics, and gabapentin), epidural steroid injection, and physiotherapy are used for this condition but high quality evidence on the effectiveness and safety of these nonsurgical treatments is absent either [7].

Currently, the population of seniors over 65 years of age accounts for 11.8% of the entire population, and the medical expenditures of these age groups account for 32.2% of the total expenditure in Korea. The rate of aging in the population is continuously increasing, and the incidence and prevalence of LSS are expected to increase in the future along with the general aging trend. As a result, a considerable increase in the social and economic costs is predicted. Considering this situation, effective and safe interventions are necessary for patients with LSS in Korea [8].

Nonsurgical Korean integrative interventions, including herbal medication, acupuncture, and manual therapy (Chuna), have been used for various spinal conditions, including nonspecific low back pain [9, 10] and lumbar radiculopathy [11]. Currently, however, there is no concrete evidence on the benefits and harms of these nonsurgical, conservative interventions. For spinal stenosis, only observational studies are available [12]; as a result, well-designed clinical trials will be necessary to evaluate the clinical evidence for these interventions.

This study is a pilot clinical trial on nonsurgical Korean integrative treatments for treating LSS. In this study, we will assess the feasibility of the integrated treatment protocol and study design for a randomized, conventional standard treatment, controlled trial for use in a future full-scaled clinical trial.

## 2. Methods

### 2.1. Study Objectives

The purpose of this study is to assess the feasibility of RCTs on clinical effectiveness and safety of the four-week Korean integrative treatment program for severe spinal stenosis, comparing different types of Mokhuri treatment programs and the usual care in conventional medicine in inpatient units. Information related to the compliance of the study design and interventions, the implementation of outcome assessments, and the sample size calculation for the full sized RCTs will be analyzed in this study. The null hypothesis of the primary outcome is that the change of 0-to-100 visual analogue scale (VAS) for low back pain and leg pain before and after treatment will be the same in the following three patient groups: Mokhuri treatment program group 1 (MT1 group) that will be treated with herbal medication, Chuna, acupuncture, and patient education; Mokhuri treatment program group 2 (MT2 group) that will be treated with Chuna, acupuncture, and patient education; or the usual care group that will be treated with analgesics, epidural steroid injection, and physiotherapy.

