### 2.2. Methods

This study is a corporative clinical study with Spine Center of Mokhuri Oriental Medical Hospital, Korea Institute of Oriental Medicine, and Complementary and Integrative Medicine Program of Mayo Clinic. The study design was developed through discussion among the three organizations, and the clinical study will be conducted in Mokhuri Hospital. The study protocol was approved by the Institutional Review Board of Mokhuri Hospital (MHNBH-14001). A total of 36 LSS patients with intractable symptoms that did not subside by at least three months of conventional treatment will be recruited through advertisements in newspapers and websites for these patient communities. This is a pilot study for future, full-scaled clinical trials. As a result, 12 patients will be recruited for each group without a sample size calculation for the minimum participant number according to statistical analysis of their basic information, considering possible dropouts. Because patients with both spinal stenosis and spondylolisthesis and therapeutic responses of spinal stenosis with and without spondylolisthesis are expected to differ, we will recruit 2 patients with spondylolisthesis into the 12 participants of each group to assess the difference in the clinical outcomes. The study will be conducted at the Spine Center of Mokhuri Hospital, Seoul, South Korea. In the clinical research information service (CRIS, a representative clinical trials registry platform in Korea), the protocol was registered before the first participant is included (registration number: KCT0001218). Any patients who meet the inclusion criteria and provide written informed consent for participation in the study will be randomly allocated into one of three groups, the MT 1, MT 2, or usual care groups. For sequence generation, stratified random numbers for whether the patients do or do not have spondylolisthesis will be generated using the SAS 9.2 package software. Opaque sealed envelopes will be used to conceal which group patients have been allocated to. Over a period of four weeks, each treatment will be offered in the inpatients unit. Patients will be urged to visit the research center for follow-up evaluation at three and six months after the four weeks of treatments.

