### 2.6. Outcomes

The primary outcomes are 0-to-100 VAS for low back and leg pain. The secondary outcomes are Oswestry Disability Index (ODI); EQ-5D; Roland-Morris Disability Questionnaire (RMDQ); Oxford Claudication Score (OCS); physical function tests, including treadmill tests, assessment of the walking duration, and distance without leg pain; radiologic testing; and adverse events. Every outcome variable will be assessed before and after treatment, and follow-up will continue for up to 6 months in all groups (Table 1).

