
### 2.7. Feasibility Assessment

Recruitment rate and dropout rate during the study period will be assessed for evaluating the feasibility of the study design. Reasons for the dropouts will be analyzed. Compliance to the offered treatment interventions and outcome assessment will be evaluated based on the compliance rate of participants as well as qualitative analysis on the outcome assessors' experiences. For future full-scaled RCT, we will calculate sample size based on the study result.

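### The stated purpose is feasibility, but the only primary outcomes and the only hypothesis are efficacy comparisons that 12 patients per arm can settle only if the differences are very large

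*Protocol article*

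**What the plan says.** **Purpose.** Section 2.1 opens: "The purpose of this study is to assess the feasibility of RCTs on clinical effectiveness and safety" of the four-week programme. The last paragraph of section 1 and the Discussion agree: this is a pilot meant to inform a later full-scale trial.

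**Hypothesis.** The same paragraph of section 2.1 then states the only hypothesis in the article. It begins "The null hypothesis of the primary outcome is that the change of 0-to-100 visual analogue scale (VAS" and says that this change "before and after treatment will be the same in the following three patient groups".

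**Primary outcomes.** Section 2.6: "The primary outcomes are 0-to-100 VAS for low back and leg pain". The Abstract says the same. The secondary list holds disability, quality of life, walking, imaging and adverse events.

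**Feasibility measures.** Section 2.7: "Recruitment rate and dropout rate during the study period will be assessed". It adds reasons for dropout, compliance with treatment and assessments, and a qualitative account from assessors. None of these is in the primary or secondary list.

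**Size.** Section 2.2: "12 patients will be recruited for each group without a sample size calculation for the minimum participant number", with the remark "considering possible dropouts" but no assumed rate.

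**Analysis.** Section 2.8 plans ANCOVA of change, with baseline as covariate and group as a fixed factor. No significance level, SD or target difference appears anywhere in the article.

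**The concern.** The outcome labelled primary, and the hypothesis attached to it, determine how a trial is reported. Here both concern efficacy, while the purpose is to learn whether a larger trial can be run. A report that follows the article's own ranking would lead with whether pain change differed between arms and leave the feasibility results unranked.

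The efficacy question is also one that 12 per arm answers poorly. A non-significant result could be read as showing no difference from usual care, although it would be the likely result even for a moderate true effect. A significant result could be read as proof of efficacy, although significant estimates from a trial this small tend to be too large. Setting 12 per arm without a calculation is no fault in a pilot; the fault is tying a confirmatory-style null to that number.

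**Working it through.** There is no power calculation to reproduce. The only stated figure, 3 × 12 = 36, adds up.

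**Inputs from the article:** three arms, 12 per arm, two primary pain scales, ANCOVA on change with baseline as covariate (sections 2.1, 2.2, 2.6, 2.8).

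**Assumptions:** two-sided 5%; correlation of 0.5 between baseline and post-treatment score; all 36 analysed; SD between 15 and 30 mm where millimetres are given. d is the true difference in SD units.

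**1. Precision of a pairwise difference.** Residual df = 36 − 3 − 1 = 32. Half-width = t(0.975; 32) × √(2/12) × √(1 − 0.5²) = 2.037 × 0.408 × 0.866 = 0.72 SD. At an SD of 15, 20, 25 and 30 mm this is about 11, 14, 18 and 22 mm.

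**2. Pairwise power.** Noncentral t, with noncentrality d / (√(2/12) × 0.866) and 32 df for ANCOVA, or d / √(2/12) and 22 df for an unadjusted t-test.

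| d | ANCOVA, correlation 0.5 | Unadjusted t-test |
|---|---|---|
| 0.4 | 20% | 16% |
| 0.5 | 28% | 22% |
| 0.6 | 38% | 29% |
| 0.8 | 59% | 47% |

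**3. Difference detectable with 80% power.** Without gain from the baseline covariate, the pairwise figure is 1.20 SD. For the overall three-arm F test (2 and 32 df), the largest gap between arms must be 1.15 SD if one arm differs from the other two, or 1.33 SD if the arms are evenly spaced. With a baseline correlation of 0.5 the F-test gaps shrink by the factor 0.866, to about 1.00 and 1.15 SD.

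**4. False-positive risk over the two primary scales.** Section 2.1 states one null of equality across all three groups for each scale, and section 2.8 enters group as one factor, so the plan as written is one overall test per scale. For independent scales, 1 − 0.95² = 9.8%. By simulation, a correlation of 0.7 between the scales lowers this to about 8.5%. Six unadjusted pairwise tests (two scales × three pairs) would give about 23% at correlation 0 and 20% at 0.7.

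**5. What 36 patients give on feasibility.** As an illustration, 32 of 36 retained (89%) has an exact 95% CI of 74% to 97%; 29 of 36 (81%) has 64% to 92%. The pooled SD (33 df) has a 95% CI of 0.81 to 1.32 times its estimate. These quantities serve the stated purpose.

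**The case against.** The best defence is that feasibility is not neglected. Section 2.7 is devoted to it, the Abstract mentions it, and the Discussion says the findings will serve the feasibility assessment. The pain scores also serve part of the purpose: section 2.1 includes planning the sample size of the full trial and checking that outcomes can be collected, and both need these data. Naming the later trial's candidate primary outcome in a pilot is reasonable. All of this stands. It is a reason to keep collecting and reporting the pain scores, but it does not explain why a null of equality is the only hypothesis or why no feasibility measure is ranked.

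Four stronger readings are tempting, and the article does not support them.

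- *The trial cannot detect anything.* Too absolute: gaps of about 1.15 to 1.33 SD, or somewhat less with a useful baseline covariate, are detectable.
- *The plan carries a 20% to 23% false-positive risk.* This needs six unadjusted pairwise tests, which the article does not plan for the primary outcomes. The between-group t-test in section 2.8 directly follows the sentence on baseline characteristics.
- *The trial will announce an accept-or-reject verdict on efficacy.* The article gives no significance level, decision rule or efficacy claim. The risk comes from the ranking and the null, not from a stated intention.
- *An inflated pilot effect will size the full trial.* Section 2.7 says only that the calculation will rest on the study result, which may equally mean the SD and dropout. If the observed effect were used, the harm would be real: with a true d of 0.5, significant unadjusted t-test results average about d = 1.1 by simulation, which would cut the planned size to (0.5/1.1)² ≈ 0.21 of what is needed. The article leaves this open.

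**Conclusion.** The point holds as a mismatch within the article, and that part needs no assumption: the purpose is feasibility, the only primary outcomes and the only hypothesis are efficacy comparisons, and the feasibility measures have no rank. The declared primary result therefore does not answer the stated purpose.

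The size of the problem with the efficacy test does rest on assumptions (two-sided 5%, baseline correlation 0.5, no loss of patients). On that basis moderate differences would usually be missed, estimates would be uncertain by about 0.72 SD either way, and the two planned overall tests would carry a false-positive risk of about 8.5% to 10%. A lower baseline correlation or dropouts would weaken the test; a higher correlation would help it. The plan should be changed, because the change is nearly free and affects what the trial can legitimately conclude.

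**What to change.** - **Section 2.1:** remove the null hypothesis.
- **Sections 2.1 and 2.6:** name recruitment, dropout, and compliance with treatment and with assessments as the primary (feasibility) outcomes, each with a 95% CI. Keep the two pain scores as clinical outcomes and describe them as candidate primary outcomes for the full trial.
- **Section 2.7:** state that the full trial's sample size will use the pilot SD and dropout together with a clinically justified difference, not the effect observed in the pilot.
- **Section 2.8:** report ANCOVA-adjusted differences between arms with 95% CIs as exploratory, and state that no efficacy conclusion will be drawn from p-values.

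**Cost:** rewording of four sections and an update of the registry entry. No new data, visits or patients are needed and treatment is unchanged. The trial gives up a nominal efficacy claim. A smaller change, removing the null and calling the comparisons exploratory, would prevent most of the misreading but would still leave the stated purpose without a primary outcome.

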### 2.2. Methods

This study is a corporative clinical study with Spine Center of Mokhuri Oriental Medical Hospital, Korea Institute of Oriental Medicine, and Complementary and Integrative Medicine Program of Mayo Clinic. The study design was developed through discussion among the three organizations, and the clinical study will be conducted in Mokhuri Hospital. The study protocol was approved by the Institutional Review Board of Mokhuri Hospital (MHNBH-14001). A total of 36 LSS patients with intractable symptoms that did not subside by at least three months of conventional treatment will be recruited through advertisements in newspapers and websites for these patient communities. This is a pilot study for future, full-scaled clinical trials. As a result, 12 patients will be recruited for each group without a sample size calculation for the minimum participant number according to statistical analysis of their basic information, considering possible dropouts. Because patients with both spinal stenosis and spondylolisthesis and therapeutic responses of spinal stenosis with and without spondylolisthesis are expected to differ, we will recruit 2 patients with spondylolisthesis into the 12 participants of each group to assess the difference in the clinical outcomes. The study will be conducted at the Spine Center of Mokhuri Hospital, Seoul, South Korea. In the clinical research information service (CRIS, a representative clinical trials registry platform in Korea), the protocol was registered before the first participant is included (registration number: KCT0001218). Any patients who meet the inclusion criteria and provide written informed consent for participation in the study will be randomly allocated into one of three groups, the MT 1, MT 2, or usual care groups. For sequence generation, stratified random numbers for whether the patients do or do not have spondylolisthesis will be generated using the SAS 9.2 package software. Opaque sealed envelopes will be used to conceal which group patients have been allocated to. Over a period of four weeks, each treatment will be offered in the inpatients unit. Patients will be urged to visit the research center for follow-up evaluation at three and six months after the four weeks of treatments.

### 2.3. Inclusion Criteria

Patients who are aged 19 to 77 years with clinical symptoms and signs consistent with LSS, including low back pain, radicular leg pain, or leg discomfort when standing or walking, will be included in the study. The patients should have experienced claudication or radicular leg symptoms for at least one year and lack symptomatic relief from pain; also, function related to LSS should be experienced after at least three months of sufficient conservative nonsurgical treatments, including epidural injection therapy, administration of analgesics, and (or) physiotherapies. He or she needs to be diagnosed with LSS through CT or MRI and have been recommended for decompression and (or, additionally) fusion surgery by neurosurgeons or orthopedic doctors. Neurogenic claudication should appear within five minutes of walking on a treadmill with a speed of at least 1.5 miles/hour. Finally, the patient should not have been treated with an epidural injection during the last 1 month.

### 2.4. Exclusion Criteria

Patients with at least one of the following conditions will be excluded from this study:
past or present existence of a movement disorder and orthopedic problems that might affect the ability to ambulate,moderate to severe arthritis of the knee or hip that might severely compromise ambulation,past or present lower extremity peripheral vascular disease or vascular claudication,previous LSS surgery,serious concomitant medical illness (i.e., heart disease, renal failure, and active hepatitis),another specific spinal disorder (e.g., ankylosing spondylitis, infection, metabolic diseases, or severe osteoporosis),presence of major or progressive neurological deficit, including dementia,severe systemic diseases, including coronary artery disease or malignancy,any past or present psychiatric conditions, including depression and others,current usage of narcotic analgesics, including a transdermal patch,present digestive disorders including gastritis, gastric ulcer, and irritable bowel syndrome.
Anyone who is currently pregnant or plans to be pregnant will be excluded.Anyone who appears likely to encounter difficulties in adhering to this protocol as a result of noncompliance with treatments (less than 80% of treatment participation), visits, and responding to questionnaires will be excluded.

### 2.5. Intervention

Patients will be allocated into one of three groups, the MT 1, MT 2, or usual care groups, during four weeks in the inpatient unit. Patients in the MT 1 group will receive integrative treatments, including herbal medications, Chuna, acupuncture, and patient education. Those in the MT 2 group will receive Chuna, acupuncture, and patient education without herbal medication. Those in the usual care group will be offered conventional nonsurgical treatments with analgesics, epidural steroid injection, and physiotherapy. Any concomitant therapies for lumbar stenosis will be prohibited during the four-week treatment period in all patients.

In the MT 1 group, herbal medication (Gang-Chuk Tang) will be offered during the participation period. Gang-Chuk Tang (110 g), which is an herbal decoction agent consisting of* Eucommiae Cortex, Achyranthis Radix, Cibotii Rhizoma, Sorbus commixta, Geranium thunbergii, Saposhnikovia Radix*, and* Acanthopanacis Cortex*, will be administered three times a day for four weeks. Chuna is a specific manipulation technique in Korean medicine, which consists of mobilization within the limits of passive range of joint motion and muscle relaxation according to the patient's respiration [13]. In this study, we will perform relaxative Chuna using Ergo style TM FX.-5820 Table (Chattanooga Group, USA); the detailed methods are presented in the following list. 

*Steps for the Chuna Technique*
Patients are laid on the table in the prone position. Patients need to relax and breathe slowly.Ergo style COX table is set to work for automatic flexion and distraction of the lumbar vertebra. The flexion angle is adjusted to the patient's condition (within 5 to 15 degrees), and it should not surpass the pain threshold of the patients. The autoflexion speed needs to be adjusted according to the breathing speed.The physician gently pulls and pushes rigid back muscles, including the latissimus dorsi, rhomboid, quadratus lumborum, gluteus medius and minimus, and paraspinal muscles, during autoflexion of the COX table.When the lumbar vertebrae are in flexion, the gaps in the intervertebral spaces can be manually broadened through fixing both hands of the physician at the lamina of the upper vertebra and spinous process of the lower vertebra. The patients should breathe out slowly.Steps (3) and (4) continue from the lumbar vertebra to thoracic vertebra.General lumbar roll manipulation is applied in both sides of the lumbar vertebra. Patients need to be laid on the table in the lateral recumbent position.Patients will attend approximately ten minutes of Chuna treatment. For acupuncture therapy, 0.25 × 40 mm disposable stainless steel needles will be used. LI4, ST36, LV3, BL22, BL23, BL24, BL25, and Ashi points will be selected for acupuncture. The depth of insertion will be 1.5 to 30 mm for each point applied to induce “deqi sensation.” Acupuncture needles will be retained for approximately 15 minutes. A certified Korean medicinal doctor who has over 10 years of clinical experience will offer Chuna and acupuncture treatment five times per week over a period of four weeks. Patient education, which consists of teaching precautions related to daily activity and walking training methods, will be conducted through face-to-face counseling with the physician five times a week over a period of four weeks. The patients will be offered standard education information (see the following list).

*Patient Education Information*

*General Notes*
The patients are to relax in bed, because of the possibility that they will experience symptoms in the incubation period that they might not feel prior to the treatment during the first week of treatment.From the second week of the treatment, the patients must practice simple movements such as moving the lower limbs, head, or shoulders slightly to the left and to the right according to the instructions of the medical team. In particular, it will be necessary to compare the symptoms patients experience for a week of treatment on a weekly basis. In addition, the patients should be able to accurately compare and be aware of their neurologic claudication and pain as well as that experienced during the early morning period of relieving tension.In cases of maladaptive treatment-related symptoms (e.g., extreme pain continuing for more than a month that does not respond to appropriate medications, disorders of urinary and fecal continence, and sudden loss of function or sensation in the lower limb), it will be necessary to proceed to surgical intervention to prevent secondary neurological damage.

*Cautionary Notes regarding Walking Training or Routine Walking *
Walking time is to be adjusted according to the conditions of the patient. However, adjustments will be required in the walking time from 10 to 20 minutes and thus patients may need to rest by suspending the exercise in cases of pain.During the first week of treatment, patients may experience symptoms in the incubation period and hence may need to rest by limiting their exercise level to the minimum.During the second week of treatment, the patients shall increase their walking distance for 20 m after two to three days depending on each patient's individual situation.After the end of treatment sessions, the patients must increase their walking time by one minute every three days for two to three months and must aim to walk routinely for approximately one half hour without pain.

*Cautionary Notes for Exercise*
Intensive exercise must be avoided. Excessive rotational movement of the lumbar or cervical vertebrae increases the load onto slipped disks, leading to further pain exacerbation. Therefore, the exercise regimen must be properly adjusted according to the orders of the medical team.The lumbar and cervical vertebral exercises conducted by our hospital shall be performed via a predetermined frequency (moving the head to the left and the right, shrugging the shoulders, and exercising the lower limb, 20 repetitions for 5 sets). Care must be taken not to excessively increase the repetitions.

*Notes regarding Movements in Activities of Daily Living*
When lifting objects, use the knees as much as possible. Patients should avoid lifting excessively heavy objects and should also avoid performing work in a crouched position.During the treatment period and for two to three months after the treatment sessions, patients shall limit their sitting time (not more than 10 minutes at a time). Excessive strenuous exercise shall be avoided.In circumstances wherein patients must maintain a seated position, such as when eating a meal, patients must avoid an Indian-style seated position and must relieve the burden on the lumbar region by having the legs out of bed.

*Notes regarding Work*
The work load must be reduced as much as possible during the treatment period. In cases requiring the unavoidable processing of work duties, the time devoted to computer use must be reduced.The use of electronic devices such as computers or smart phones for long periods may cause pain in the cervical vertebral and lumbar areas. Therefore, the use of these devices must be avoided as much as possible.Patients in the MT 1 group will be offered an herbal decoction, Chuna, acupuncture therapy, and patient education, while those in the MT 2 group will be offered Chuna, acupuncture therapy, and patient education during the treatment period.

In the usual care groups, conventional conservative treatments for LSS will be offered [14]. Drugs, including muscle relaxants, NSAIDs, gabapentin, and limaprost, will be prescribed by the neurosurgeon and will be continued during the four weeks. Epidural steroid injections will be offered three to four times in the inpatient unit. Physiotherapy, including 10 to 20 minutes of treatment with a heating pad (STEMKOREA Co., Korea), transcutaneous electrical nerve stimulator (TENS, Homer Ion Laboratory Co. Ltd., Japan), and deep tissue heating therapy (Radio Derm, RoboMax Co., Korea), will be applied at the affected region once a day for five days a week over a period of four weeks. A neurosurgeon will prescribe medications and inject patients with an epidural steroid injection for symptom relief. A physiotherapist will conduct the physiotherapy.

